#### Secondary outcomes

Fasting plasma glucose, A1c, total cholesterol, LDL cholesterol, HDL cholesterol, triglycerides, high-sensitivity C-reactive protein, blood pressure, and AUCs for glucose and glucagon during OGTT comprise secondary outcomes. Quality of life, assessed with the SF-36v2 questionnaire (standard version), satiety quotient (see below), experience with the dietary patterns and change in medication are also included as secondary outcomes.

### Anthropometric measurement and laboratory tests

Trained nurses and investigators will perform the lab tests and anthropometric measurements in the Hospital Insular de Lanzarote. All measurements and laboratory tests will follow standard certified methods [34].

Standing height without shoes will be measured with a height stadiometer. Height will be reported to the nearest 1 mm.

Weight will be measured using an electronic weighing scale placed on a hard surface with the patient in the fasting state. Patients will be asked to take off their shoes, jackets, sweaters, and any other heavy clothing, and to remove all heavy items from their pockets. Then the patients will place both feet in the center of the platform and distribute their weight evenly between both feet. Weight is reported to the nearest 0.1 kg.

Waist circumference will be measured using a measuring tape immediately above the iliac crest. Measurements will be reported to the nearest 0.1 cm.

The hip circumference will be measured using a measuring tape at the level of the trochanter major and reported to the nearest 0.1 cm.

Sagittal abdominal diameter will be measured using a sagittometer (that is, a sliding beam caliper with a ruler) in the sagittal plane during a normal expiration at the level of iliac crest (L4 to L5) with the subject in supine position on a firm bench with the knees bent. Measurements will be reported to the nearest 0.1 cm.

Blood pressure will be measured in the upper arm (preferably right arm) at the level of the heart after five minutes rest in the sitting position (MONICA criteria) [34]. Ideally, the same person should perform all measurements in the same patient, using the same sphygmomanometer and procedure. The mean of two measurements will be calculated as the final result.

Skinfold measurements will be taken by use of a validated caliper with a precision of 0.2 mm. The following points will be measured as follows:

•tricipital skinfold: in the posterior part of the arm in the middle point between the lower border of the acromion and the vertex of the olecranon.

•bicipital skinfold: in the anterior part of the arm in the middle point between the most external and superior border of the acromion and the most external and superior of the radial bone head.

•suprailiac skinfold: approximately 2.5 cm above iliac crest in mid-axillary line.

•subscapular skinfold: in the inferior vertex of the scapular bone.

### Four-day weighed food records and satiety scores

A four-day weighed food record, including one weekend day, with weighing of each food item on an electronic weighing scale (that could be set to zero), will be completed by the participants before the start and end of each intervention period (Figure 1). By completing each four-day weighed food record, participants will be asked to rate, on a scale from 0 to 100, how well the record represents their food habits in the preceding four weeks. Nutrient compositions will be assessed with the nutritional software package DIAL [32] used to create the meal plans. In parallel with the four-day weighed food records, the participants will record their subjective rating of satiety by means of a seven-point Likert-type scale (Figure 1). Satiety Quotients will be calculated, as the intra-meal quotient of change in satiety during meal and consumed energy or weight of food and drink for that specific meal.

### Data management

Study data will be collected and managed using REDCap™ (Research Electronic Data Capture) electronic data capture tools hosted at Lund University [35]. REDCap™ is a secure, web-based application designed to support data capture for research studies, providing: 1) an intuitive interface for validated data entry; 2) audit trails for tracking data manipulation and export procedures; 3) automated export procedures for seamless data downloads to common statistical packages; and 4) procedures for importing data from external sources.

REDCap™ will be configured according to the study protocol in a way that the researchers can register all data at baseline, 4, 10 and 14 weeks after study start. Only the researchers and the hospital nurses will have access to REDCap™. This web application allows for management of the trial without violation of privacy or participant confidentiality and integrity of allocation concealment. The procedure also facilitates supervision from abroad by some of the investigators.

### Data analysis

Differences in baseline characteristics between the participants will be measured using two-tailed unpaired *t*-tests. A two-tailed paired *t*-test will be used to analyze treatment effects within subjects and a two-tailed unpaired *t*-test will be used to compare mean values of outcome variables between the two diets. Normal Q-Q plots and Shapiro-Wilk test will be performed to check for normal distribution of data. Data transformation will be applied in case the data does not present normal distribution. To test for a possible period effect a two-tailed unpaired *t*-test comparing the mean difference between first and second period for outcome variables and food intake will be performed. To test a possible carry-over effect a two-tailed unpaired *t*-test comparing the average of observations for outcome variables and food intake between the two periods will be performed. *P* < 0.05 will be considered to indicate statistical significance.

Analysis will be conducted by use of SPSS for Mac Version 20 (IBM SPSS Statistics for Mac, Version 20.0. Armonk, NY: IBM Corp.)

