### Power calculations

The predefined primary outcomes are changes in fasting fructosamine and glucagon. In order to detect, with 80% power and at a significance level of 5%, a 26 μmol/L larger reduction in fructosamine after diet B than after diet A, 12 subjects are estimated to be required. For a 37 ng/L difference in change in fasting glucagon between the diets, 13 subjects are estimated to be required.

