### Evaluation

Before and after each intervention period, an oral glucose tolerance test (OGTT) will be performed in the morning after obtaining venous blood samples in the fasting state, and measurements of blood pressure, height (only at the start of intervention 1), weight, waist and hip circumference, sagittal abdominal diameter, triceps, biceps, suprailiac and subscapular skinfolds, at the start and end of both intervention periods will also be taken. The participants will ingest 75 grams of glucose and blood samples will be drawn for glucose and glucagon at 0, 15, 30, 60, 90 and 120 minutes. Areas under the curve (AUC) for plasma glucose (AUC glucose) and glucagon (AUC glucagon) will be calculated. Of great consequence, and for safety reasons, we will assess capillary glucose, using a glucometer, before performing the OGTT. If the result is greater than or equal to 190 mg/dL (10.5 mmol/L) the OGTT will not be performed. Information about participants’ quality of life will be assessed by means of the short form quality of life questionnaire SF-36v2 (standard version), using the validated Spanish version, which will be filled by the participant during each of the OGTT procedures. During the OGTT, at the end of each intervention period, patients will also be asked to give written answers to three open-ended questions about their experience with the dietary pattern that they have been following during the previous four weeks, specifically: ‘What are your thoughts about this diet?’, ‘Describe your positive and negative experiences with this diet’ and ‘How do you think this diet has affected your health?’

During both dietary interventions, free lunch will be provided every day in the kitchen of the Hospital Insular de Lanzarote. Here, our objective is two-fold: a) to control nutrient intake as much as possible and b) to give the participants behavioral support during visits to the hospital.

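### The paired t-test for treatment effects has no named contrast: read as start-to-end change within a diet, it does not test whether the diets differ; read as A versus B, it duplicates the unpaired test

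*Protocol article*

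**What the plan says.** One sentence under Data analysis gives out two tasks. The first goes to a paired t-test, described in these words: "will be used to analyze treatment effects within subjects and a two-tailed unpaired". The second goes to the unpaired t-test on which that quote breaks off; according to the article, this one "will be used to compare mean values of outcome variables between the two diets". The pair of values entering the first test is not named. One threshold covers every test in the section: P "< 0.05 will be considered to indicate statistical significance".

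Under Power calculations, the question is a difference between diets. For fructosamine the target is "a 26 μmol/L larger reduction in fructosamine after diet B than after diet A", and for glucagon it is a 37 ng/L "difference in change in fasting glucagon between the diets, 13 subjects are estimated to be required". Under Primary outcomes, both are measured at the start and end of each four-week period, so the data allow either a start-to-end pairing or an A-versus-B pairing. The Discussion gives the aim as a comparison of two healthy diets.

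**The concern.** On the natural reading, each primary outcome gets a start-to-end P-value for diet A, another for diet B, and a between-diet P-value. The first two carry the label of treatment effect, but their null is that the mean does not move over four weeks.

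That null can be false for reasons that say nothing about a difference between the diets. Both diets are designed to be healthy and both are classed as very healthy by the nutritional software. In both periods a daily hospital lunch is provided, partly "to give the participants behavioral support during visits to the hospital". There is no untreated period against which a shared change could be set.

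A result in which diet B is significant and diet A is not would be easy to take as support for the food-choice hypothesis. It can arise often when the diets are equally effective. The abstract says that the results will be used to judge the need for larger and longer studies, so such a misreading could affect a decision.

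**Working it through.** **1. The plan's own figures.** The article states 12 subjects for 26 μmol/L of fructosamine and 13 for 37 ng/L of glucagon, "with 80% power and at a significance level of 5" per cent. No standard deviation is given, so these numbers cannot be reproduced independently. They can be back-solved. For a two-sided paired t-test on the between-diet difference in change, 80% power with n = 12 allows an SD of differences up to about 29.2 μmol/L (26/29.2 = 0.89 SD). With n = 13 it allows up to about 43.7 ng/L (37/43.7 = 0.85 SD). The stated numbers thus fit plausibly with a between-diet contrast.

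**2. Rejection rate of a start-to-end test.** Let δ be the mean change on a diet and σ the SD of that change. The t statistic is noncentral t with n − 1 degrees of freedom and noncentrality √n × δ/σ. With n = 13 the critical value is 2.179.

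| Shared change δ/σ (assumed) | Noncentrality | One within-diet test rejects |
|---|---|---|
| 0 | 0 | 5.0% |
| 0.25 | 3.606 × 0.25 = 0.90 | 13% |
| 0.5 | 3.606 × 0.5 = 1.80 | 38% |

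**3. Exactly one diet significant when the diets are equal.** If a person's two changes are uncorrelated, the probability is 2p(1 − p):

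- δ/σ = 0.25: 2 × 0.132 × 0.868 = 0.23
- δ/σ = 0.5: 2 × 0.382 × 0.618 = 0.47

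Simulation with correlation ρ between the two changes extends this:

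| δ/σ | Exactly one, ρ = 0 / 0.3 / 0.5 | At least one, ρ = 0 / 0.3 / 0.5 | Paired B minus A |
|---|---|---|---|
| 0.25 | 23% / 20% / 18% | 25% / 23% / 22% | 5% |
| 0.5 | 47% / 39% / 33% | 62% / 58% / 55% | 5% |

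By symmetry, about half of the cases with exactly one significant diet favour diet B.

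**4. The same check in the plan's units.** For fructosamine take n = 12 and the back-solved SD of differences of 29.2. The SD of one diet's change is 29.2/√(2(1 − ρ)): 20.7 at ρ = 0, 29.2 at ρ = 0.5 and 37.8 at ρ = 0.7. With equal diets, one within-diet test rejects as follows (ρ from 0.7 to 0):

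| Common change (μmol/L) | Rejection rate |
|---|---|
| 0 | 5.0% |
| 2.6 | 5.5% to 6.8% |
| 6.5 | 8.5% to 16.9% |
| 13 | 19% to 51% |
| 26 | 59% to 98% |

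Glucagon at the same fractions of 37 ng/L gives almost the same rates.

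**5. The other reading.** If the paired test is diet A versus diet B in the same person, it rejects about 5% of the time whatever the common change. The planned unpaired test of the same contrast rejects about 5% at ρ = 0 and about 1% at ρ = 0.5, because it ignores the pairing. The two tests would then answer one question with different P-values.

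**The case against.** The strongest objection is textual. The article never says that the paired test compares start with end, or that it is run within each diet. In a cross-over, a within-subject treatment effect ordinarily means A versus B in the same person, and that test is sound. This stands, so the start-to-end reading is an inference. It is the more natural one only because the same sentence gives the diet comparison to the unpaired test. The alternative does not rescue the sentence, since it leaves two tests for one contrast.

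A reader might infer that the plan has an inflated type I error. The documents do not support that. A start-to-end test holds 5% for its own null, and rejecting when the mean has truly moved is correct. It becomes a false positive only if it is used to claim that the diets differ. No section says it will be, and the test assigned to that comparison does not exceed 5% in these checks.

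A reader might also blame the shared change on regression to the mean after selection on A1c. That is weak: A1c is a screening measurement and neither primary outcome, and the baseline laboratory tests come later. Nor are all the shared influences non-dietary. Improvement because both diets are healthy is a diet effect; it is simply not a difference between them.

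Finally, an article may leave detail to a fuller document. Here, however, the article does state the tests, and what it states does not identify the effect being tested.

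**Conclusion.** The point holds in conditional form. The article labels a paired test as the treatment effect without naming its contrast. On the natural reading the label does not fit the trial's question; on the other reading the between-diet contrast has two competing tests.

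The size rests on an assumed change common to both diets, which the documents do not give. At 0.25 to 0.5 SD with 13 completers and ρ from 0 to 0.5, each within-diet test rejects 13% to 38% of the time and exactly one diet is significant 18% to 47% of the time, with equally effective diets. With no shared change each test rejects at 5%, and with a small one (2.6 μmol/L of fructosamine) at 5.5% to 6.8%. What follows is that within-diet P-values cannot stand as treatment effects in the trial's sense. It does not follow that the planned diet comparison is too liberal, or that the investigators intend to use within-diet significance to compare the diets.

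**What to change.** In Data analysis, define the treatment effect on fructosamine, glucagon and the secondary outcomes as the within-person diet B minus diet A difference in change. Test it within subjects with allowance for period, in place of the unpaired t-test. Report start-to-end changes within each diet descriptively, as means with 95% confidence intervals, and do not call them treatment effects. A statement that significance on one diet but not the other will not count as evidence of a difference would be a useful addition, but it is secondary.

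The cost is a few sentences of wording, with no extra patients or measurements. Allowing for period takes one degree of freedom (with 13 completers, 11 instead of 12). The trial gives up before-after significance claims for each single diet; without an untreated comparison, such claims could not separate a diet's effect from other changes over the period.

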### Design

The ADILAN study is a randomized cross-over open label dietary intervention trial in patients with T2DM who will be instructed to eat two different dietary patterns during two four-week periods separated by a six-week washout period. The procedure for screening, eligibility and recruitment is detailed in Figure 2. Schedule of enrollment, interventions and assessments can be found in Additional file 1. Detailed information about enrollment, interventions and assessments is described in Additional file 2.

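### The between-diet comparison is specified as an unpaired t-test, although in this cross-over both diets are measured in the same participants

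*Protocol article*

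**What the plan says.** The Design section describes a "randomized cross-over open label dietary intervention trial" in patients "who will be instructed to eat two different dietary patterns during two four-week periods separated by a six-week washout period". Each completer therefore supplies data on diet A and on diet B.

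Power calculations names the endpoints: "The predefined primary outcomes are changes in fasting fructosamine and glucagon". The trial is sized "with 80% power and at a significance level of 5"% on the difference between the diets in those changes. The result is 12 subjects for 26 μmol/L in fructosamine; for 37 ng/L in glucagon, "13 subjects are estimated to be required". The section gives no SD, no within-person correlation and no test. The Participants section enrols 15 to allow for one or two drop-outs.

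Data analysis gives two tests in one sentence. The first part reads "A two-tailed paired *t*-test will be used to analyze treatment effects within subjects". The second part reads "a two-tailed unpaired *t*-test will be used to compare mean values of outcome variables between the two diets". Period and carry-over effects are each tested separately, also with unpaired t-tests.

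**The concern.** The primary question is diet A against diet B, and the test assigned to that comparison treats the two sets of values as coming from different people. With 13 completers it would handle 26 values as 26 independent participants. Independence is false by design, so the standard error is wrong unless the within-person correlation happens to be zero.

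The paired test does not clearly repair this. Since the between-diet comparison goes to the unpaired test, the natural reading is that the paired test covers start-to-end change within one diet. If it is instead meant as A against B, the plan has two conflicting tests for its primary question and does not say which decides.

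At stake are a P value that may not mean what it claims and, on some assumptions, a real diet effect that is missed.

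**Working it through.** **Inputs from the protocol.** Differences to detect of 26 μmol/L (N = 12) and 37 ng/L (N = 13), with 80% power at 5% (Power calculations); two-tailed tests at P < 0.05 (Data analysis).

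**Assumptions.** SD and correlation are not given. The SD is back-solved, and the correlation ρ is varied from -0.3 to 0.8.

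**Step 1: the plan's own figure.** N of 12 and 13 cannot be reproduced forward without an SD. Solving backward with the noncentral t distribution (two-sided 5%, 80% power):

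- Paired test: the standardised difference must be 0.889 at n = 12 and 0.847 at n = 13. The SD of the within-person difference in change is then 26/0.889 ≈ 29 μmol/L and 37/0.847 ≈ 44 ng/L.
- Unpaired test with 12 or 13 values per diet: per-diet SD of 21.7 μmol/L and 32.3 ng/L.
- N split as two parallel groups: SD of 14.5 μmol/L and 21.7 ng/L.

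Each basis fits the stated N with a suitable SD, so the document neither confirms nor excludes any of them.

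**Step 2: what ignoring the pairing does.** Let σ be the per-diet SD. The true variance of the mean difference is 2σ²(1 - ρ)/n, while the unpaired test estimates 2σ²/n. Its standard error is therefore wrong by a factor 1/√(1 - ρ):

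- ρ = 0.5: 1/√0.5 = 1.41, too large
- ρ = 0.3: 1/√0.7 = 1.20, too large
- ρ = 0: 1, correct
- ρ = -0.3: 1/√1.3 = 0.88, too small

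**Step 3: size, if 12 and 13 were computed for a paired comparison.** The SD of the difference is held at the paired values from step 1, so σ = SD of difference/√(2(1 - ρ)). For fructosamine at ρ = 0.5 this is 29.3/√1 = 29.3 μmol/L. The unpaired test was applied to 100,000 simulated data sets per setting (fructosamine, n = 12 / glucagon, n = 13):

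| ρ | Type I error, % | Power, % |
|---|---|---|
| -0.3 | 8.31 / 8.45 | 89.1 / 88.9 |
| 0 | 5.05 / 5.08 | 83.7 / 83.3 |
| 0.2 | 3.03 / 2.99 | 77.3 / 76.9 |
| 0.3 | 2.23 / 2.23 | 72.1 / 71.7 |
| 0.5 | 0.92 / 0.86 | 57.0 / 56.0 |
| 0.7 | 0.15 / 0.15 | 29.8 / 29.2 |
| 0.8 | 0.04 / 0.02 | 13.5 / 12.8 |

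A paired test has 80% in every row by construction. At ρ = 0 the unpaired test is slightly ahead because it has more degrees of freedom (2 × 12 - 2 = 22 against 12 - 1 = 11). Power drops below 80% once ρ exceeds about 0.1.

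**Step 4: size, if 12 and 13 were computed for an unpaired test.** With per-diet SD 21.7 and 32.3, the unpaired test has its nominal 80%. A paired analysis of the same data would have about 76% at ρ = 0, 89% at 0.3 and 96-97% at 0.5.

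**The case against.** The strongest reply is that the loss of power is not shown. A reader might infer that the stated 80% is not delivered, or that 13 people could suffice only because each is their own control. Neither follows. Both inferences need a sample size computed on a paired basis, and the first also needs a clearly positive correlation; the document gives neither. Step 1 shows that an unpaired basis fits the same numbers. The sized endpoint is a change score, which subtracts each person's stable level, so its correlation between periods may be near zero; there the unpaired test loses nothing. High correlations are plausible for raw levels (an assumption), but they cannot be combined with SDs back-solved for changes. This reply stands, and it makes the power statement conditional.

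A second reply is that the standard two-period cross-over t-test is itself unpaired. That is true, but it compares within-person period differences between the two sequence groups. The text says the comparison is between diets, so this does not rescue it.

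Third, a reader might infer that period is ignored altogether. It is not: Data analysis tests it separately, and Randomization uses minimization with starting diet as a weighting variable. With near-balanced sequences, a period shift largely cancels from the mean diet difference and mainly adds variance. What remains is the lesser point that the diet comparison itself carries no period adjustment, although the Intervention section has everyone start together.

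Finally, a reader might infer that a go/no-go decision hangs on this P value. The abstract says only that the results will help to assess the need for larger studies; no rule is tied to the test.

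**Conclusion.** The between-diet test is wrong as written. It contradicts the design on the primary question, and its nominal 5% error holds only at zero within-person correlation. On the simulated range the type I error runs from about 8% at -0.3 to about 2.2% at 0.3 and 0.9% at 0.5. Reading the paired test as the A-against-B contrast does not clear the plan; it only turns the defect into two tests for one question.

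The power consequence is conditional. If the sizing was paired, power is about 83-84% at correlation 0, 72% at 0.3, 56-57% at 0.5 and 29-30% at 0.7. If the sizing was unpaired, the stated power is not contradicted, but a within-person analysis would gain considerably at positive correlation. The protocol does not let a reader choose between these cases. The figures rest on back-solved SDs, normally distributed data with equal variance under both diets, and an assumed range of correlations. A within-participant analysis respects the design on either reading.

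**What to change.** In Data analysis, replace the unpaired between-diet test with a within-participant comparison of the change in each primary outcome, adjusted for period. Two equivalent forms for complete data are:

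- For each participant take the change in period 1 minus the change in period 2, and compare these differences between sequences AB and BA with a two-sample t-test. Half the difference between the sequence means estimates the diet effect.
- Fit a mixed model with diet and period as fixed effects and participant as a random effect.

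Report the mean diet difference with its 95% CI. State that the paired test of start-to-end change within one diet, if kept, is descriptive and does not answer the primary question.

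In Power calculations, state the test and SD actually used to obtain 12 and 13. If that test is not the within-participant one, restate the power for it. The authors should report the basis they used, not adopt one after the fact.

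The cost is one paragraph of text and one degree of freedom for period (13 - 2 = 11 instead of 13 - 1 = 12 with 13 completers). No new patients or measurements are needed.

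### The diet A versus diet B comparison is assigned to an unpaired t-test although both sets of values come from the same people

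*Protocol article*

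**What the plan says.** The Design section describes a randomised cross-over in which each patient follows "two different dietary patterns during two four-week periods separated by a six-week washout period".

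The Data analysis section names two tests in one sentence. The first part reads "A two-tailed paired *t*-test will be used to analyze treatment effects within subjects". The second reads "a two-tailed unpaired *t*-test will be used to compare mean values of outcome variables between the two diets". The section goes on to unpaired tests for period and carry-over effects. It does not describe the diet comparison as a comparison of the two sequences.

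Under Power calculations, "The predefined primary outcomes are changes in fasting fructosamine and glucagon". With 80% power and a 5% significance level, the stated requirements are "a 26 μmol/L larger reduction in fructosamine after diet B than after diet A, 12 subjects are estimated to be required" and, for the other primary, "For a 37 ng/L difference in change in fasting glucagon between the diets, 13 subjects are estimated to be required". That section gives no SD, no within-person correlation and no named test. The Participants section takes 13 as the minimum and plans to enrol 15, allowing for one or two drop-outs.

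**The concern.** An unpaired t-test treats the diet A values and the diet B values as two independent groups. Here they are two measurements on the same 13 to 15 people. The test's error term leaves out the within-person correlation, which is the quantity a cross-over is chosen to exploit.

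The direction depends on the sign of that correlation. If it is positive, the test is too conservative, intervals are too wide and real differences are harder to detect. If it is negative, the test rejects too often. Both primaries and every continuous secondary outcome compared in this way are affected. The abstract says the results will be used to judge the need for larger and longer studies, so the between-diet estimate and its precision feed directly into that decision.

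The wording adds a second problem. Treatment effects within subjects could mean the before-to-after change on each diet, or the A-versus-B contrast. On the first reading the only between-diet test is the unpaired one. On the second, each outcome has two tests that will generally give different P-values, with no rule for choosing between them.

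**Working it through.** **Inputs from the protocol.** Differences of 26 μmol/L (fructosamine) and 37 ng/L (glucagon), 80% power, 5% level, 12 and 13 subjects (Power calculations); two-tailed tests (Data analysis).

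**Assumed.** Rho between a participant's diet A and diet B values, ranged because the document gives none; equal SD s on both diets; normal data; no period effect in steps 1 to 4.

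**1. The plan's own figures.** The 12 and 13 cannot be reproduced without an SD. What can be found is the SD that each implies, using the noncentral t distribution, two-sided 5%, 80% power:

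| Basis | n | Standardised difference needed | Implied SD |
|---|---|---|---|
| Paired, n-1 df | 12 | 0.889 | 26/0.889 = 29.3 μmol/L (within-person difference) |
| Paired, n-1 df | 13 | 0.847 | 37/0.847 = 43.7 ng/L (within-person difference) |
| Unpaired, 2n-2 df, n values per diet | 12 | 1.197 | 26/1.197 = 21.7 μmol/L (per diet) |
| Unpaired, 2n-2 df, n values per diet | 13 | 1.145 | 37/1.145 = 32.3 ng/L (per diet) |

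Nothing in the document says which basis was used.

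**2. Error term.** The true variance of the mean B-minus-A difference is 2s²(1-rho)/n. The unpaired test estimates 2s²/n. Its standard error is therefore too large by a factor 1/√(1-rho) if rho is positive, and too small if rho is negative.

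**3. Calibration at n = 13** (simulated bivariate normal pairs; nominal 5%, two-sided). The interval ratio, unpaired to paired, is t(24 df)/t(12 df) × 1/√(1-rho) = (2.064/2.179)/√(1-rho) = 0.947/√(1-rho). That gives 1.13 at rho 0.3 and 1.34 at rho 0.5. The ratio of average simulated widths, shown below, is about 0.01 higher.

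| rho | True type I error, unpaired test | Average interval width relative to paired |
|---|---|---|
| -0.2 | 7.2 to 7.3% | 0.87 |
| 0 | 5.0% | 0.96 |
| 0.3 | 2.1 to 2.2% | 1.14 |
| 0.5 | 0.8 to 0.9% | 1.35 |

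This result does not depend on how 12 and 13 were derived.

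**4. Power at n = 13 for the 37 ng/L difference, under each sizing basis.**

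| rho | Paired sizing: unpaired test | Paired sizing: paired test | Unpaired sizing: unpaired test | Unpaired sizing: paired test |
|---|---|---|---|---|
| 0 | 83% | 80% | 80% | 76% |
| 0.3 | 72% | 80% | 84% | 89% |
| 0.5 | 56% | 80% | 87% | 97% |

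Fructosamine at n = 12 is nearly the same: under paired sizing the unpaired test has 84%, 72% and 57%.

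**5. Period.** With 13 completers the sequences split 7 and 6 at best. If period 2 shifts values by p, the person-level difference is d + p in one sequence and d - p in the other. Its simple mean is d + (7p - 6p)/13 = d + p/13. With 15 it is d + p/15. A two-sample test of within-person period differences between sequences removes this term. Its standard error with a 7/6 split is 0.5 × √(1/7 + 1/6) = 0.278 SDs of the within-person difference, against 1/√13 = 0.277 for the paired test. With 11 df its power is about 79% where the paired test has 80%.

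**The case against.** Three points on the other side have force.

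- **Power.** A reader might infer that the stated 80% is not what the planned test delivers. The document does not support that as a fact. If 12 and 13 came from an unpaired calculation, the unpaired test meets or exceeds 80% at rho of zero or above. Even under paired sizing it has 83% at rho zero. The shortfall is conditional.
- **Size of rho.** A reader might go on to rho of 0.7 to 0.9, where under paired sizing the unpaired test's power falls to 29% and below. The Power calculations section and the abstract define the primaries as changes, although the Primary outcomes section omits the word. Subtracting each period's starting value already removes stable differences between people, so correlations that high cannot be presumed. At rho zero the test is correctly calibrated.
- **The paired test.** A reader might say that the unpaired test is the only one named for A versus B. The paired test in the same sentence can be read as the within-person contrast, in which case a valid test is already planned and the defect is that two tests compete.

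An unpaired test can also be valid in a cross-over when it compares within-person period differences between the two sequences. The sentence does not describe that: it compares mean values between diets. Finally, with positive correlation the error is conservative, so in a pilot it costs sensitivity more than it risks false claims.

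These points limit how large the consequence can be said to be. They do not make an independent-samples comparison of the two diets fit the design.

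**Conclusion.** The point holds as a mismatch between test and design. As written, the between-diet comparison ignores the pairing, and its P-values and intervals are correct only if rho is near zero. Under normality and equal SDs, with 13 completers, the nominal 5% becomes about 2% at rho 0.3, just under 1% at rho 0.5 and about 7% at rho -0.2. The role of the paired test in the same sentence is ambiguous, and either reading needs a correction.

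No claim that the trial is underpowered follows. Over rho from 0 to 0.5 the unpaired test's power runs from 83% down to 56% or from 80% up to 87%, depending on a sizing basis that the document does not state. For positive rho of 0.3 or more, the within-person test has the higher power on both bases.

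**What to change.** In Data analysis, replace the unpaired between-diet test with one within-participant analysis of change on diet B minus change on diet A. Name it as the deciding test for both primaries and use it for the continuous secondary outcomes. If the paired t-test is meant for before-to-after change within each diet, say so and label it descriptive.

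Because 13 or 15 participants cannot divide equally between sequences, prefer a form that allows for period: a two-sample t-test of within-person period differences between the two sequences, or a cross-over model with participant and period effects. A paired t-test is the simple alternative if no period effect is assumed.

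In Power calculations, state the test and the SD of the within-person difference behind 12 and 13 (29.3 μmol/L and 43.7 ng/L if the calculation was two-sided and paired). If they were derived for another analysis, restate the power.

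The cost is a few sentences, with no new data and no extra participants. The degrees of freedom fall from 24 to 12 at n = 13 (11 with the sequence comparison). That loses about 3 to 4 points of power if rho is zero, and about one more point for the period adjustment.
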